#### Pre-implementation phase

We will first assess baseline rates of insurance coverage, cancer screening, and general recommended preventive care across all study arms and the matched controls. We will also assess rates of these outcomes across the total OCHIN population to compare to the recruited clinics. Additional analyses including patients from all CHCs in OCHIN will be conducted to assess the impact of recent policy changes on insurance coverage and cancer preventive care. Data for these analyses will be extracted from the OCHIN EHR and will include demographic information (i.e., age, federal poverty level, race/ethnicity, language spoken), insurance coverage dates and types, as well as cancer screenings (e.g., fecal occult blood test (FOBT) orders, colonoscopy and mammography referrals, and pap smear receipt), immunizations (e.g., human papillomavirus (HPV) vaccination), cancer-related health behavior assessment and counseling (e.g., smoking screening and intervention and obesity screening and intervention), and receipt of general recommended preventive care (e.g., blood pressure, glucose, and lipid assessments). This information will be extracted using standardized codes for diagnoses, labs, medications, procedures, and referrals, and electronically collected vital signs and social history (e.g., smoking status) from visits. As seen in Table 2, we will define receipt of cancer screenings and prevention based on services with an A–B rating from the US Preventive Services Task Force and recommendation from the Advisory Committee on Immunization Practices [45, 46]. Our EHR dataset will also contain additional information about the use of health services such as encounter information, provider data, clinic location, reason for visit, level of service, and type and number of visits.

**Table 2 Tab2:** Description of outcome measures

Dependent variable	Description/measure for preventive care
Insurance coverage	Covered at visit (yes, no); all visits covered vs. not covered; percent of visits covered
Insurance continuity	Months covered by Medicaid; percentage of time covered by Medicaid
Recommended preventive care services (NQF)	Breast cancer screening^a^ (0031), NCQA; currently used by MU1, HEDIS®, and MACS
	Cervical cancer screening^a^ (0032), NCQA; currently used by MU1, HEDIS®, and MACS
	Colorectal cancer screening^a^ (0034); MU1, HEDIS®
	Tobacco use screen and medical assistance with tobacco cessation^a^ (0027), NCQA; currently used by MU1, HEDIS®, and MACS
	Obesity screening and counseling^a^

*NQF* National Quality Forum (www.qualityforum.org), *MACS* Medicaid Adult Core Set (www.medicaid.gov/Medicaid-CHIP-Program-Information/By-Topics/Quality-of-Care/Downloads/Medicaid-Adult-Core-Set-Manual.pdf), *NCQA* National Committee for Quality Assurance (www.ncqa.org), *MU1* Meaningful Use Stage 1 of the Medicare & Medicaid Electronic Health Record Incentive Program (www.cms.gov/Regulations-and-Guidance/Legislation/EHRIncentivePrograms/CQM_Through_2013.html), *HEDIS®* Health Employer Data and Information Set (www.ncqa.org/HEDISQualityMeasurement.aspx), *USPSTF*
www.uspreventiveservicestaskforce.org/Page/Name/uspstf-a-and-b-recommendations/

^a^USPSTF A or B recommendation

Additionally, we will conduct an informational phone call with relevant clinic staff (e.g., clinic manager, insurance eligibility specialists) at all intervention sites to learn about the clinic workflows for providing insurance assistance and any other factors that may affect how a clinic implements and uses the insurance support HIT tools. We will share findings from the pre-implementation calls with the HIT tool development team to inform tool development and refinements. These calls will also inform the development of trainings and practice facilitation for Arm II sites. In addition, we will hold a retreat with CHC staff, patient advisors, project advisors and consultants, and policymakers to aid in refining the health insurance support HIT tools. At the retreat, we will utilize user-centered design processes to better understand users’ needs and wants with regard to product design and utilization of the HIT tools [47]. These processes will enable us to interactively share the first version of the tools and develop a work plan and timeline for further refinements. A health literacy expert will assess the reading demands and document complexity of all patient communication materials (e.g., automated e-mails) to ensure that content is appropriate for the CHC patient population.

#### Implementation phase

The HIT tools will be implemented in both study arms, but the arms will differ in the levels of training, facilitation, and implementation support received, as described below.

##### Arm I

Study training materials (e.g., a PowerPoint presentation covering tools and study purpose, a tool guide, sample best practice workflow) will be made available to the clinics in Arm I for independent training via the OCHIN learning management system (LMS). LMS is a software application for the management of documentation, tracking, reporting, and delivery of electronic educational technology, education courses, and training programs.

##### Arm II

In addition to the study training materials provided for Arm I, we will provide interactive trainings for Arm II clinics to explain the insurance support HIT tools, prepare clinic staff for using the tools, and assist clinics in revising workflows to maximize tool utilization. A practice facilitator will be available to the clinic staff and will continue to engage actively with tool users over the course of the implementation phase, including on-site, face-to-face trainings and support.

We will assess the use of the insurance support HIT tools as well as the facilitation process in Arm II qualitatively and quantitatively. We will conduct brief, semi-structured phone interviews with key informants from each Arm II clinic and the facilitator periodically to monitor tasks and workflows related to health insurance support and other factors that may affect how a clinic implements the HIT tools. The goal is to understand what is and is not working regarding the HIT tools, any changes in workflow that might impact insurance support tool use, and experiences with the practice facilitation process. We anticipate conducting 5–10 interviews with each clinic in Arm II. Findings may be used to guide and modify the facilitation process in Arm II and possibly future refinements to the insurance support tools.

### Overview of effectiveness component of the trial

An independent biostatistician used propensity score matching [39] to identify the control group of 23 CHCs that most closely match the intervention clinics on clinic and patient characteristics that have the potential to confound the insurance support HIT tools’ effect on health insurance coverage rates and cancer screening. An OCHIN team member identified 64 clinics in three states that were eligible for the study’s control group and matched based on the state of the organization, the total number of patients in 2014, and the percentage of uninsured visits, female gender, and Medicaid beneficiaries. The 23 control clinics were selected in a 1:1 ratio based on the nearest available match from the intervention clinics. The intent was to achieve the optimal overall balance in the matching characteristics between the intervention and control groups. Balance diagnostics were performed to assess whether the propensity score model had been properly specified [48].

### Post-implementation assessment

After implementation of the insurance support HIT tools, we will assess the effectiveness of these tools and the implementation support strategies using qualitative and quantitative methods.

#### Post-implementation quantitative assessment

We will compare post-implementation insurance coverage and cancer screening and prevention rates across all study arms and in the matched control groups. We will also assess insurance coverage and receipt of general recommended preventive care/cancer screening and prevention across the entire OCHIN population. Study outcome variables are described below (also see Table 2).

#### Post-implementation qualitative assessment

Based on data collected during the implementation period, we will purposively sample CHC sites to participate in site visits. At the site visits, we will evaluate the implementation process, how the HIT tools are being used by clinics and how workflows around insurance are changing, and facilitators and barriers to implementing and using the HIT tools. Based on the quantitative data (described above), we will explore differences between high and low performers across arms.

During each site visit, the research team will spend 3–5 half-days observing clinic operations that are pertinent to use of the insurance support HIT tools. This will include observing all operational areas (e.g., scheduling/check-in, provider encounters) where insurance issues arise and are addressed. The team will also opportunistically conduct informal interviews with clinic staff, as informal interviews often elicit different and more insightful information than is captured during formal interviews. Between 5 and 10 interviews will be conducted at each site. Researchers will prepare field notes, share observations, and strategize for additional data collection opportunities.

If quantitative analyses reveal that control clinics have significantly improved rates of coverage, similar to the intervention clinics, we will employ ethnographic methods to better understand what is contributing to their improvements.

### Study measures

#### Study measures for the effectiveness component of the trial

Our *outcome measures* (presented in Table 2) are patients’ health insurance status and continuity rates and receipt of recommended cancer screenings and prevention (i.e., cervical, colorectal, and breast cancer screening, HPV vaccination, and smoking and obesity screening and intervention). Outcomes will be measured individually and in combination. For example, we will measure if cancer screening services were received within appropriate intervals and also the overall rate of indicated services received.

The primary *independent variable* is provision of insurance support HIT tools (i.e., intervention clinics with tools, control clinics without tools). Potential *confounder variables* in multivariable analyses will include patients’ demographic information (e.g., age, federal poverty level, race/ethnicity, language spoken, rural/urban location). We will also collect additional information from the EHR about the use of health services such as encounter information, provider data, clinic location, level of service, types of visits, and number of visits.

#### Study measures for the implementation component of the trial

The primary independent variable is study arm (Arm I: tool + basic training vs. Arm II: tool + enhanced training + facilitation). The primary outcome measures are directed by the widely accepted RE-AIM (Reach, Effectiveness, Adoption, Implementation, Maintenance) framework for evaluation of implementation success [49]. Reach will involve rates of insured patient visits and rates of insurance continuity. Effectiveness will refer to rates of patients receiving guideline-concordant cancer screening and other preventive care. Adoption will pertain to patterns, frequency, and timing of insurance support HIT tools usage by clinic staff and patients. Implementation will relate to users’ perceptions (perceived ease of use, usefulness of receiving information about health insurance), and acceptance of the tools (intention to use and satisfaction with the tools). Maintenance will involve all of the above measures over time. Some of these outcomes overlap with those of the effectiveness component of the trial.

### Analytic strategy

#### Quantitative analysis of the effectiveness component of the trial

We will estimate pre- and post-implementation rates of insurance coverage and cancer screenings for clinics in the intervention group and the matched control group. For each patient in the study population, we will determine continuity of coverage and receipt of age- and gender-appropriate recommended cancer screening and preventive care 18 months pre- and 18 months post-intervention. The intervention group will be compared with the matched control group using a difference-in-differences (DID) approach. We will utilize generalized linear/non-linear mixed models, which offer flexible regression modeling to accommodate different sources of correlations (serial and intra-clinic), categorical and continuous covariates, and fixed and time-dependent covariates. This general model allows us to study a wide range of dependent variables, including logistic regression (binary data), beta regression (percent data), Poisson regression (count data), and Gaussian regression (normally distributed data). For example, we will use a random-effect logistic regression model to analyze insurance continuity at pre- and post-intervention periods (dependent variables) as a function of whether a patient belongs to a control or intervention CHC (primary independent variable) and other possible confounders. Serial and intra-clinic correlations will be modeled as random effects.

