### Overview of implementation component of trial

#### Intervention sites

An OCHIN team member identified 99 clinics in 32 eligible health center organizations within OCHIN. Of those invited, 23 clinics in 7 health center organizations agreed to participate (23 % of eligible clinics) and 76 clinics in 25 organizations declined (77 % of eligible clinics). The 7 participating organizations are located in 3 Medicaid expansion states (Oregon, California, and Ohio). These organizations varied in size; the number of primary care clinic sites per organization ranged from 1 to 6. Due to the possible correlation among clinic sites in the same organization, an independent biostatistician randomized the 23 clinics by service organization. A covariate-constrained cluster randomization [44] was used to balance the number of clinics between the two treatment arms. The randomization was balanced using the following covariates: state the organization was located in (Oregon vs. non-Oregon), total number of patients per organization, and percentage of uninsured patients per organization. The biostatistician and research team members were blind to the clinics during randomization. Once randomized, the study team was given the list of clinics participating in each study arm (11 in Arm I and 12 in Arm II).

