#### Quantitative analysis of the implementation component of the trial

Similar to the effectiveness aspect of the trial, we will compare the pre- and post-intervention rates of patients’ insurance coverage and receipt of recommended cancer screenings using DID generalized linear/non-linear mixed models comparing Arm I and Arm II. Moreover, post-implementation, we will assess and compare use of the tools across the study arms, including information such as who uses which tools and functions, as well as frequency and timing of use. This will help identify individual- and clinic-level factors associated with more frequent use of the health insurance support HIT tools.

To evaluate tool use, we will assess monthly data (e.g., percent of patient charts with evidence of tool use) in regression models to estimate associations between use and patient panel characteristics. Additionally, we will describe and compare the characteristics of patient encounters with tool use vs. those with no tool use, via random-effect logistic regression models that assess associations between use of the insurance support HIT tools (dependent variables) and socio-demographic characteristics (independent variables) and other possible confounders.

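### Seven organizations were randomized, but the stated mixed models stop at the clinic level, so Arm I vs Arm II standard errors are too small if organizations differ in pre-post change

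*Protocol article*

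**What the plan says.** All statements are in the protocol article.

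- **Intervention sites** gives the clusters: "23 clinics in 7 health center organizations agreed to participate", and "the number of primary care clinic sites per organization ranged from 1 to 6". The unit of assignment and its reason are explicit: "Due to the possible correlation among clinic sites in the same organization", "an independent biostatistician randomized the 23 clinics by service organization". The result is "11 in Arm I and 12 in Arm II". The number of organizations in each arm is not given.
- **Quantitative analysis of the effectiveness component** names the dependence that the models handle. They are chosen to "accommodate different sources of correlations (serial and intra-clinic"; the parenthesis closes there, with two sources listed. The section ends with the commitment "Serial and intra-clinic correlations will be modeled as random effects".
- **Quantitative analysis of the implementation component** describes its approach as similar to the effectiveness analysis, "using DID generalized linear/non-linear mixed models comparing Arm I and Arm II". It adds no further level of clustering.

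No section brings organization into the analysis, whether by a random effect, a cluster-robust variance or a randomization-based test.

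**The concern.** The design and the analysis disagree about what the independent unit is. The design treats the organization as that unit and gives within-organization correlation as the reason. The analysis names its correlation sources twice and stops at the clinic both times. An analysis written from this text would treat 23 clinics as separately assigned when 7 organizations were.

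Arm I vs Arm II is the only randomized contrast; the tools-versus-no-tools comparison uses propensity-matched controls. Facilitation and workflow changes could well be shared across the clinics of one organization. A single organization may supply 6 of an arm's 11 or 12 clinics, that is, half or more of it. A chance difference between a few organizations could then be reported, with a confidence interval that is too narrow, as an effect of facilitation.

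**Working it through.** **Inputs from the article.** 7 organizations, 23 clinics, 1 to 6 clinics per organization, 11 vs 12 clinics by arm. The counts agree with each other: 11 + 12 = 23 clinics, 23 + 76 = 99 eligible clinics, 7 + 25 = 32 eligible organizations. The article states no power, alpha or intraclass correlation, so there is no figure of its own to reproduce.

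**Assumptions.** rho is the share of between-clinic variance in pre-post change that lies between organizations. Organization sizes are not listed. Exactly 19 sets of seven sizes have minimum 1, maximum 6 and sum 23, and all allow an 11/12 split. The illustrative layout is 1, 2, 3, 3, 4, 4, 6.

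**Step 1: variance of the arm contrast.** For organization sizes m, the true variance relative to the variance with independent clinics is

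[(1 − rho)(1/11 + 1/12) + rho(Σm²/121 + Σm²/144)] / (1/11 + 1/12),

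with the first sum over the 11-clinic arm and the second over the 12-clinic arm. One split of the illustrative layout is 6 + 4 + 1 = 11 and 4 + 3 + 3 + 2 = 12:

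- Σm² = 36 + 16 + 1 = 53, and 53/121 = 0.438.
- Σm² = 16 + 9 + 9 + 4 = 38, and 38/144 = 0.264.
- 1/11 + 1/12 = 0.1742, and 0.702/0.1742 = 4.03.
- Ratio = (1 − rho) + 4.03 rho.

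At rho = 0.10 the ratio is 0.90 + 0.403 = 1.30, so the clinic-level standard error is too small by a factor of √1.30 = 1.14. At rho = 0.50 the ratio is 0.50 + 2.015 = 2.51, a factor of 1.59. Across 18 size sets with 3 vs 4 organizations and an 11/12 split, the ratio runs 1.15–1.19 at rho = 0.05, 1.29–1.37 at 0.10 and 2.47–2.85 at 0.50.

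**Step 2: rejection of a true null.** Clinic-level changes were simulated with no arm effect and tested by a two-sided 5% t test that ignores organization (21 df).

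| rho | Illustrative layout | Mean over 18 layouts |
|---|---|---|
| 0 | about 5% | 4.9% |
| 0.05 | about 7% | 7.1% |
| 0.10 | about 9% | 9.0% |
| 0.30 | about 16% | 18.0% |
| 0.50 | about 24% | 26.4% |

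A t test on the 7 organization means rejects 3.9% to 4.8% of the time over the same rho range, so it holds the nominal level.

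**Step 3: reference distribution.** Seven organizations in two arms leave 7 − 2 = 5 df (t = 2.57), against 23 − 2 = 21 df for clinics (t = 2.08). This alone widens an interval by 2.57/2.08 = 1.24.

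**Step 4: what a permutation test could show.** Over the 19 size sets, 6 to 28 allocations give an 11/12 split in either direction. If that split was enforced, the smallest two-sided p lies between 2/28 = 0.07 and 2/6 = 0.33. Further balance constraints could only reduce the number of allocations.

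**The case against.** The strongest counter-argument is that the size of the problem rests on rho, which the article does not give. It speaks only of possible correlation among clinics, not of correlation in their changes, and DID removes stable differences between organizations. At rho = 0 the clinic-level test is nominal, and at rho = 0.02 it rejects only about 5.7% of the time. This stands: the result is conditional, and a reader who concludes that the error rate is certainly well above 5% goes beyond the text.

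It is also fair that the random-effects sentence sits in the effectiveness section and reaches Arm I vs Arm II only through the word similar. That is still the natural reading, and nothing in the implementation section alters it.

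A third defence is that model detail belongs in an analysis plan that is not shown. This does not dispose of the point, because the article is not silent: it states the correlation structure and omits the unit it randomized.

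Other inferences are tempting but unsupported:

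- **Clinic intercept only.** A reader might infer that the models have only a clinic intercept, so that precision comes almost wholly from patient numbers. The text names serial random effects too and does not say intercept-only.
- **Balancing covariates unused.** A reader might infer that state, size and percentage uninsured are left out of the analysis. The confounder list is given by example and allows for others.
- **A confirmatory test.** No alpha and no confirmatory 5% test is stated for Arm I vs Arm II.

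**Conclusion.** The point holds in conditional form. The stated analysis omits the level at which the trial randomized, although the article gives correlation at that level as its reason for randomizing there. If organizations differ in pre-post change, standard errors for Arm I vs Arm II are too small. The rejection rate of a nominal 5% clinic-level test then moves from about 5% at rho = 0 to about 7%, 9%, 16% and 24% at 0.05, 0.10, 0.30 and 0.50. These rates assume clinic-level change scores and the illustrative organization sizes; other admissible sizes give similar values.

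Organization also matters in principle for the 23 vs 23 effectiveness comparison, because the intervention clinics come from 7 organizations. No size can be given there: the article does not say how many organizations supply the controls, and that comparison is not randomized.

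**What to change.** - **Arm I vs Arm II:** add random effects for organization and organization-by-period to the clinic and serial effects, or analyse organization-level changes. With 7 organizations the fuller model may be hard to estimate, and the organization-level analysis is then the simpler route.
- **Inference:** use small-sample degrees of freedom, about 5, and report the contrast as an estimate with an organization-level confidence interval.
- **Supplement, if wanted:** a permutation test over the acceptable allocations of the constrained randomization, with a note that it may be unable to reach 0.05 if the 11/12 split was enforced.
- **Effectiveness comparison:** account for organization there as well.

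The cost is some analysis wording, a few model terms and wider confidence intervals. Trial status reports randomization as complete and implementation as still ahead; the change needs no new sites or data.
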